**Month 1**
• FIQ
• Sociodemographic variables: 1 question (current work situation)
• Pharmacological and non-pharmacological treatment received during the last month
**Month 2**
• FIQ
• Sociodemographic variables: 1 question (current work situation)
• Pharmacological and non-pharmacological treatment received during the last month
**Month 6**
• FIQ
• Sociodemographic variables: 1 question (current work situation)
• Pharmacological and non-pharmacological treatment received during the last four months
• CSRI-adapted version: use of healthcare and social services during the first six months (0–6 months)
• EuroQoL-5D
**Month 12**
• FIQ
• Sociodemographic variables: 1 question (current work situation)
• Pharmacological and non-pharmacological treatment received during the last six months
• CSRI-adapted version: use of healthcare and social services during the first six months (6–12 months)
• EuroQoL-5D

### Variables and instruments of measurement

The study protocol was approved by the research ethics committee of the Foundation Jordi Gol i Gorina (Barcelona) and consists of the following materials:

1. *Sociodemographic characteristics*: Gender, birth date, address, marital status, education level, work status.

2. *History of the illness*: age of onset, date of the first diagnosis, pharmacological treatments (oral antidepressants, benzodiazepines-hypnotics, muscular relaxants and non-steroid analgesic and anti-inflammatory medications) and non-pharmacological treatments (physical exercise, relaxation techniques, cognitive-behavioural therapy) received during the previous 6 months.

3. *Questionnaire on chronic medical condition*.

4. *Fibromyalgia Impact Questionnaire (FIQ-Spanish version) *[23]: Instrument that measures physical function, work, and well-being, and contains visual analogue scales (VAS) for pain, sleep, fatigue, stiffness, anxiety and depression. A total score may be obtained after normalization of some items (between 0–10) and adding them to the VAS. Total scores range between 0–80 (without job items), with a higher score indicating a negative impact.

5. *EuroQoL-5D questionnaire (EQ-5D – Spanish version) *[22]: Generic instrument of health-related quality of life. It has two parts: Part 1 records self-reported problems in each of five domains: mobility, self-care, usual activities, pain/discomfort and anxiety/depression. Each domain is divided into three levels of severity corresponding to no problems, some problems, and extreme problems. Part 2 records the subject's self-assessed health on a Visual Analogue Scale (VAS); it is a vertical 10 cm line on which the best and worst imaginable health states score 100 and 0, respectively.

6. *Client Service Receipt Inventory – adapted (CSRI – Spanish version) *[24]: questionnaire for collecting information about use of healthcare and social care services, other economic impacts (such as time off work due to illness) and socio-demographic information. The variant used in this study was designed to collect retrospective data on service utilisation during the first and last six months after the beginning of the treatment.

### Intervention program

Participants from the intervention group will undergo a multi-component psycho-educational program that deals with FM based on available scientific evidence. It includes measures and instruments that can be employed within the Catalan Primary Health Care, whereas the participants from the control group will receive only the treatment prescribed by their physician.

The intervention program consists of nine 2-hour sessions delivered during a two month period. Participants will be allocated in groups with a maximum of 18 subjects per group. All sessions will take place at the PC centres Gava-2 or Viladecans-2. The contents of each session are displayed in Table 2.

**Table 2 T2:** Summary of the intervention program.

**Session 1: **General information. Expectations of the patients. History of the illness. Principal and secondary symptoms in FM. Physiological mechanisms involved in the genesis of pain.
**Session 2: **Relaxation training-I
**Session 3: **Diagnosis. Pharmacological and non-pharmacological treatments. Prognosis. Current model of health care in Catalonia. Units specialized in the treatment of FM.
**Session 4: **Relaxation training-II
**Session 5: **Strategies to increase self-esteem and regulate emotions. Pain experience and recurrent invalidation. Social support (family and friends).
**Session 6: **Relaxation training-III
**Session 7: **Holistic medicine
**Session 8: **Relaxation training-IV
**Session 9: **Benefits of physical exercise in FM. Qualitative assessment of the intervention program. Resolving doubts. Discussion concerning the strengths and weaknesses of the intervention.

In order to avoid conversations concerning the psycho-educational program among patients from different groups, we will remind the participants from the intervention of the condition that they are not allowed to talk about the program with those persons that are not attending their group. Before baseline assessment, an explanatory note addressing this important issue will be delivered to the patients participating in the program.

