**Method/Design:**

*Design*. Randomized controlled trial with a 12-month follow-up involving two groups, one of which is the intervention group that includes patients receiving a psychoeducational program and the other the control group consisting of patients treated for FM in the usual way.

*Setting*. Three urban PC centers in the province of Barcelona (Spain).

*Sample*. The total sample comprises 218 patients (over 18 years of age) suffering FM, selected from a database (Rheumatology service-Viladecans Hospital) of patients with this illness. Only those patients introduced in the database between the years 2005 and 2007 were included in the selection. Selected patients will be asked for written informed consent to participate in the study.

*Intervention*. Multi-component program including information about the illness, counselling about physical exercise and training in autogenic relaxation. The intervention consists of nine 2-hour sessions delivered during a two-month period. The pharmacological treatment prescribed by the physician was maintained in both groups.

*Main variables*. Sociodemographic characteristics, quality of life, use and cost of healthcare and social services.

*Measures*. Quality of life is to be measured with the FIQ and the EuroQol-5D, and the use of healthcare services with an adapted version of the Client Service Receipt Inventory (CSRI). These variables will be measured before the beginning of the program (baseline) and 1, 2, 6 and 12 months later.

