### Data collection and ethical aspects

First, patients that meet the inclusion criteria will be phoned by a research assistant who is a psychologist. Second, the research assistant will make an appointment with those patients that agree to participate in the study. Third, written consent will be obtained before the beginning of the study. Participants will be provided with a general overview of the aims and activities of the study. They will be also informed that they may choose to drop out at any time with the guarantee that they will continue to receive the treatment considered most appropriate by their physician. Patients in the control group will receive the treatment considered most appropriate by their physician.

Results will be monitored and most of data collected by means of standard questionnaires conducted in face-to-face interview by the research assistant, who has been trained in the administration of the instruments. The research assistant does not know which study group the patients being interviewed belong to ("blind"). Follow-up assessments shall take place at 1, 2, 6 and 12 months after the inclusion of the patient (see Table 1).

**Table 1 T1:** Follow-up assessments.

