### Statistical analyses

Data collected will be analysed using SAS statistical analysis software (SAS Institute Inc. 1999. v8.0, 4th ed) and employing both quantitative and qualitative techniques.

First, the intervention and control groups will be compared in order to verify that there are no significant differences between them in socio-demographic terms, clinical baseline data, etc. We shall use mean and standard deviation (SD) in continuous variables and percentages in categorical variables. For comparisons we shall use the Student-T test for continuous variables and the Chi-square test for categorical variables. Non-parametric tests may also be used.

Given that we have one between-groups factor with two levels (2 Groups: Intervention and Control) and one within-subjects factor with five levels (Baseline and 4 follow-up assessments: 0, 1, 2, 6, and 12), a 2 × 5 mixed factorial ANOVA will be performed to study the effect of the psycho-educational program on the quality of life. Then, between-subjects planned comparisons may also be used (post-hoc comparisons with independent samples T-test). If we observe differences between groups in quality of life prior to treatment, one-way analyses of covariance will be carried out using baseline scores as a covariate). In addition, we shall carry out a logistic regression analysis taking the groups as dependent variable (the target variable is a categorical variable with two categories: Intervention and Control) and the collected measures as independent variables. This analysis will let us to know the association between the intervention and the cost of the healthcare resources, controlling for the rest of variables.

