**Figure 1 F1:**
[figure not shown]
Formulas for calculating the QALYs gained in the first and last six months after the beginning of the program.

In the Figure 1, d_0–6 _is the incremental treatment effect on change in EQ-5D utility score for the first 6 months and d_6–12_the incremental treatment effect on change in EQ-5D utility score for the last 6 months. These incremental treatment effects will be estimated using multivariate ordinary least squares regressions, adjusting for baseline differences among treatment groups. The covariates included in the models will be: age, gender, years of education, employment and marital status, baseline FIQ and EQ-5D utility scores, and type of medication prescribed. To address uncertainty in the ICUR sampling distribution, non-parametric bootstrapping with five thousand replications will be carried out for each treatment comparison [29].

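### The confidentiality note is to reach programme patients before the baseline assessment, which on its plain reading discloses allocation before baseline FIQ and EQ-5D are self-reported and can bias the analyses that use baseline

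*Protocol article*

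**What the plan says.** Under Intervention program, the article explains how talk between the arms is to be prevented: "we will remind the participants from the intervention of the condition that they are not allowed to talk about the program" with people outside their group. The next sentence gives the timing of the written notice: "Before baseline assessment, an explanatory note addressing this important issue will be delivered to the patients participating in the program". The programme belongs to one arm only: "Participants from the intervention group will undergo a multi-component psycho-educational program", while controls receive only what their physician prescribes.

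The Abstract (Method/Design) defines baseline relative to the programme, not to randomisation: "These variables will be measured before the beginning of the program (baseline) and 1, 2, 6 and 12 months later". The outcomes concerned are patient-reported: "Quality of life is to be measured with the FIQ and the EuroQol-5D". Data collection and ethical aspects lists a telephone call, an appointment and written consent, and does not say where randomisation falls. The only blinding described is the interviewer's: "The research assistant does not know which study group the patients being interviewed belong to".

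Baseline scores are used in three places:
- Statistical analyses specifies a mixed ANOVA with "one within-subjects factor with five levels (Baseline and 4 follow-up assessments: 0, 1, 2, 6, and 12" months.
- The same section adds an ANCOVA with baseline as covariate, if the groups are seen to differ before treatment.
- Under Figure 1 in Cost-utility analyses, the regressions for change in EQ-5D utility are fitted "adjusting for baseline differences among treatment groups", with baseline FIQ and EQ-5D utility among the covariates.

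**The concern.** A note that goes only to programme patients can be handed out only once it is known who they are, and receiving it tells the patient which arm they are in. If that happens before baseline, the baseline FIQ and EQ-5D are no longer pre-allocation measurements. Expectation in patients who know that they will attend the programme could move their scores either way. Blinding the interviewer does not protect a score reported by a patient who knows the allocation.

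Randomisation makes a true baseline equal between arms in expectation. That is what justifies using it as a reference level or covariate. A baseline recorded after disclosure loses that property, and any shift passes into the estimated effect. The Discussion relies on baseline comparisons to detect pre-treatment differences, but such a comparison cannot separate chance imbalance from a reaction to allocation. A reaction to allocation could even trigger the ANCOVA, which would then adjust for it as if it were chance.

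**Working it through.** **Order of events.** The note comes before baseline, goes to patients in the programme, and concerns a condition that binds intervention participants. Baseline comes before the programme starts. The time of randomisation is not given. The order that fits these statements most directly is allocation, note, baseline, session 1. No section states the reverse.

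**The plan's own figure.** Setting and study sample gives a 5-point FIQ difference, a spread of 12.1 (worded as a standard error, used here as an SD), two-sided alpha 0.05, power 0.80 and 15% dropout. Then n = 2 × (1.96 + 0.84)² × 12.1² / 5² = 91.93, so 92 per arm, and 92 / 0.85 = 108.2, so 109. The stated 109 per arm reproduces and does not depend on this point.

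**How a shift propagates.** Let b be the between-arm shift in baseline FIQ caused by disclosure, present at baseline and absent at follow-up. Let ρ be the baseline-to-follow-up correlation, with equal SDs at both times. The sizes of the biases are:
- Baseline-to-follow-up contrast in the 2 × 5 ANOVA: b.
- Group main effect in that ANOVA: b/5, because one of five levels is shifted.
- Contrasts among months 1, 2, 6 and 12, and t-tests at a follow-up visit: 0.
- ANCOVA on baseline: ρ × b.
- QALY regression, 0–6 months: change adjusted for its own baseline is algebraically an ANCOVA, so about ρ × the shift in EQ-5D utility.

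**Illustration.** The documents give neither b nor ρ. Assume b = 1 to 3 points and ρ = 0.3 to 0.7, with SD 12.1 and 92 analysed per arm. The SD of a change is 12.1 × √(2(1 − ρ)), the ANCOVA residual SD is 12.1 × √(1 − ρ²), and each standard error is that SD × √(2/92). For example, at b = 1 and ρ = 0.5 the standard error of the change contrast is 12.1 × √(2/92) = 1.78. With no true effect, the chance of a two-sided significant result is then 0.087 instead of 0.05.

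| b | ρ | Bias, change contrast | Type I error | Bias, ANCOVA | Type I error |
|---|---|---|---|---|---|
| 1 | 0.3 | 1 | 0.076 | 0.30 | 0.054 |
| 1 | 0.5 | 1 | 0.087 | 0.50 | 0.062 |
| 1 | 0.7 | 1 | 0.112 | 0.70 | 0.085 |
| 2 | 0.3 | 2 | 0.157 | 0.60 | 0.064 |
| 2 | 0.5 | 2 | 0.202 | 1.00 | 0.099 |
| 2 | 0.7 | 2 | 0.304 | 1.40 | 0.196 |
| 3 | 0.3 | 3 | 0.295 | 0.90 | 0.083 |
| 3 | 0.5 | 3 | 0.390 | 1.50 | 0.163 |
| 3 | 0.7 | 3 | 0.584 | 2.10 | 0.378 |

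Against the 5-point target, a change-contrast bias of 1–3 points is 1/5 = 20% to 3/5 = 60%. With 109 per arm, a baseline t-test would be significant, and so could trigger the ANCOVA, with probability 9%, 23% and 45% for b = 1, 2 and 3. With b = 0 there is no bias.

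**The case against.** The strongest reply is that the article never says when patients are randomised or told their arm. Intervention patients are to be reminded of a condition, so they had heard of it before, and all participants receive an overview of the study around consent. A note given then to everyone, loosely described as programme patients, would disclose nothing. A condensed article may also leave the order of enrolment steps to the full protocol. This stands in part: knowledge of allocation before baseline is a strong inference, not a statement. But the sentence does fix an order and a recipient group, and its plain reading is the harmful one. The point therefore rests on what is written, not on a missing detail.

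A second reply is that the size is assumed. That stands in full. The 20–60% figure is the assumed shift divided by 5, and the direction is unknown. A more hopeful, lower baseline in the intervention arm would understate the benefit, and a higher one would overstate it.

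A reader might also infer three stronger things that the documents do not support:
- **Every analysis using baseline is biased.** The order creates a risk; no shift is shown. The article names no FIQ change-score analysis, and the ANCOVA is only conditional.
- **The interviewer is unblinded from the first visit.** Read literally, the ban on talking outside the group covers the interviewer too, so the note may help to protect blinding.
- **Patients leave differentially before being measured.** Nothing in the article bears on this.

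**Conclusion.** The point holds as a risk of bias created by a stated sequence. On its plain reading, the Intervention program section discloses allocation to intervention patients before baseline FIQ and EQ-5D are self-reported, and no other section reverses that order. ANOVA contrasts that include baseline would carry the full shift. The conditional ANCOVA and the baseline-adjusted QALY regressions would carry roughly the shift multiplied by the correlation. Follow-up-only comparisons would carry none of it.

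The FIQ figures, 1–3 points for baseline-to-follow-up contrasts and 0.3–2.1 points for ANCOVA, rest wholly on the assumed shifts and correlations and on a shift confined to baseline. They show the mechanism and do not predict what would happen. No EQ-5D figure is offered because the documents supply nothing to base one on. The text does not support saying that patients certainly know their allocation at baseline, or that the results are certainly biased.

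**What to change.** Rewrite the sentence in Intervention program so that all baseline measures are completed before randomisation is performed and disclosed, and intervention patients receive the note afterwards, before session 1. Place randomisation explicitly in the sequence of steps in Data collection and ethical aspects.

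If a note to everyone was intended, say instead that it goes to all consenting participants before randomisation. Either wording removes the problem.

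The edit need not settle which instruments are taken at baseline. In particular, a baseline CSRI is not clearly planned: the Abstract suggests that all variables are measured then, while Variables and instruments of measurement ties the CSRI to the first and last six months after treatment begins, and Table 1 collects it at months 6 and 12.

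The cost is a reordering of existing steps and a sentence or two of text. No visit or instrument is added, and the sample size stays at 109 per arm.

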### Forecast execution dates

Initial recruitment of patients: September 2007

Deadline for recruitment of patients: November 2008

Deadline for period of patient monitoring: December 2009

Publication of results: 2010

### Statistical analyses

Data collected will be analysed using SAS statistical analysis software (SAS Institute Inc. 1999. v8.0, 4th ed) and employing both quantitative and qualitative techniques.

First, the intervention and control groups will be compared in order to verify that there are no significant differences between them in socio-demographic terms, clinical baseline data, etc. We shall use mean and standard deviation (SD) in continuous variables and percentages in categorical variables. For comparisons we shall use the Student-T test for continuous variables and the Chi-square test for categorical variables. Non-parametric tests may also be used.

Given that we have one between-groups factor with two levels (2 Groups: Intervention and Control) and one within-subjects factor with five levels (Baseline and 4 follow-up assessments: 0, 1, 2, 6, and 12), a 2 × 5 mixed factorial ANOVA will be performed to study the effect of the psycho-educational program on the quality of life. Then, between-subjects planned comparisons may also be used (post-hoc comparisons with independent samples T-test). If we observe differences between groups in quality of life prior to treatment, one-way analyses of covariance will be carried out using baseline scores as a covariate). In addition, we shall carry out a logistic regression analysis taking the groups as dependent variable (the target variable is a categorical variable with two categories: Intervention and Control) and the collected measures as independent variables. This analysis will let us to know the association between the intervention and the cost of the healthcare resources, controlling for the rest of variables.

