### Setting and study sample

Three primary health care centres (Viladecans-2, Gavà-1 and Gavà-2) in the province of Barcelona (Catalonia, Spain) voluntarily participated for the study. The sample pool (n = 530) comprises only those patients included in a FM database of the Viladecans Hospital for the years 2005 and 2006. In the event of a lack of participants, the plan is to recruit patients with FM included in the database during the year 2007.

Patients considered for inclusion will be those aged 18–75 years-old, contactable by telephone, who meet the diagnostic criteria of FM established by the ACR. The following patients will be excluded: those with a diagnosis not based on the ACR criteria, those with cognitive impairment or suffering from physical, mental/psychiatric limitations or a severe concurrent rheumatologic illness that impedes participation in the study evaluations, those who are not expected to live at least 12 months and those without schooling.

To calculate the sample size it was taken into account that we need to obtain a difference of at least 5 points in the FIQ between those that respond and those who are resistant to the intervention. The criterion of 5 points is based on two previous studies conducted with Spanish fibromyalgia patients [21,22]. A total of 109 patients per condition is needed to conduct the study, assuming an alpha risk of 0.05 and a beta risk of < 0.20 in a bilateral contrast, a standard error of 12.1 reported in a previous study [21], and a 15% dropout rate.

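### Baseline FIQ is treated as an outcome level and is adjusted for only if the arms differ before treatment; adjusting always would gain power at no cost

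*Protocol article*

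**What the plan says.** Under Statistical analyses, the arms are first compared at baseline with t and chi-square tests. For efficacy, "a 2 × 5 mixed factorial ANOVA will be performed to study the effect of the psycho-educational program on the quality of life". Its within-patient factor has five levels: baseline and months 1, 2, 6 and 12. The section does not say whether the group main effect or the group-by-time interaction is the test of efficacy. After the ANOVA, "between-subjects planned comparisons may also be used (post-hoc comparisons with independent samples T-test"; these tests make no use of baseline. Baseline becomes a covariate only on a condition: "If we observe differences between groups in quality of life prior to treatment, one-way analyses of covariance will be carried out".

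The Cost-utility analyses section does otherwise. Its regressions for the QALY effects list baseline FIQ and EQ-5D utility among the covariates with no condition attached.

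Setting and study sample gives the design figures: "a difference of at least 5 points in the FIQ", "a standard error of 12.1 reported in a previous study", "assuming an alpha risk of 0.05 and a beta risk of < 0.20 in a bilateral contrast", "and a 15% dropout rate", and the result "A total of 109 patients per condition is needed to conduct the study".

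**The concern.** In a randomised trial, a baseline difference between arms arises by chance. A test for it does not show whether baseline FIQ predicts later FIQ, and it is that prediction which makes adjustment worthwhile. A rule triggered by the test leaves a good predictor unused in about 95% of trials, and the estimator then depends on a chance result.

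Baseline is also not an outcome, because treatment cannot have affected it. Counting it as a fifth level has one of two consequences, depending on which ANOVA term is read. The group main effect averages in a visit with zero effect. The interaction is a 4-df omnibus test that gives no effect size at any visit, while the stated objective concerns quality of life at 1, 2, 6 and 12 months.

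At stake are the power and the clarity of the main analysis of the main objective.

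**Working it through.** **Inputs.** Difference 5 points, SD 12.1 (the article calls it a standard error, but read as an SD it reproduces the sample size), two-sided alpha 0.05, power 80%, dropout 15%, all from Setting and study sample. Assumptions: baseline-to-follow-up correlation r from 0.3 to 0.7; for the ANOVA, equal variances and equal correlations between visits; for the trigger, a two-sided 5% baseline test, since the article says only that a difference is observed.

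**1. The plan's own figure.** n = 2(1.960 + 0.842)² × 12.1² / 5² = 91.9, so 92 per arm. Then 92 / 0.85 = 108.2, so 109. This matches, and it corresponds to an unadjusted comparison at one visit. With 92 per arm, SE = 12.1 × √(2/92) = 1.784, 5 / 1.784 = 2.80, power 80.0%.

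**2. One visit: triggered rule against fixed ANCOVA.** Fixed ANCOVA reduces the SD to 12.1 × √(1 − r²), which is 11.54, 10.48 and 8.64 at r = 0.3, 0.5 and 0.7. For the triggered rule, let Z be the baseline z-statistic. Given Z, the unadjusted follow-up statistic is normal with mean 2.80 + rZ (rZ under the null) and variance 1 − r². Integrate its rejection probability over |Z| < 1.96, then add 5% of the ANCOVA rejection probability. Simulation of 20,000 trials per scenario agrees: 80.1%, 80.6% and 81.7% power for the rule.

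| r | Unadjusted power | Triggered rule, power | Fixed ANCOVA, power | Triggered rule, overall type I error |
|---|---|---|---|---|
| 0.3 | 80.0% | 80.4% | 83.6% | 4.8% |
| 0.5 | 80.0% | 81.2% | 89.9% | 4.3% |
| 0.7 | 80.0% | 82.0% | 97.5% | 3.6% |

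The gain from fixing the covariate is about 3, 9 and 16 percentage points.

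**3. Where the type I error goes.** When |Z| lies between 1 and 1.96 (26.7% of trials), the plan stays unadjusted despite moderate imbalance. The same integral over that range gives type I error of 7.4%, 8.2% and 8.8% at r = 0.5, 0.6 and 0.7. When |Z| < 1 (68.3% of trials) it gives 3.1%, 2.3% and 1.5%. The overall rate stays below 5%.

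**4. The 2 × 5 ANOVA, constant 5-point effect at all four follow-ups.**

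- Group main effect: the contrast is (0 + 5 + 5 + 5 + 5) / 5 = 4 points, with SE = 12.1 × √[(1 + 4r)/5 × 2/92].
- Group by time: non-central F on 4 and 728 df. The squared deviations of the effect profile from its mean sum to 16 + 4 × 1 = 20, so λ = 46 × 20 / [146.41 × (1 − r)].

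| r | Main-effect SE | Main-effect power | λ | Interaction power |
|---|---|---|---|---|
| 0.3 | 1.183 | 92.2% | 8.98 | 65.9% |
| 0.4 | 1.286 | 87.5% | 10.47 | 73.5% |
| 0.5 | 1.382 | 82.5% | 12.57 | 82.0% |
| 0.6 | 1.471 | 77.6% | 15.71 | 90.4% |
| 0.7 | 1.555 | 73.0% | 20.95 | 97.0% |

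The main effect falls below 80% from about r = 0.6 upwards, and the interaction at about r = 0.4 and below.

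**The case against.** The strongest reply is that nothing here is invalid. Unadjusted comparison is sound under randomisation, the sample size was built on it, and 109 per arm delivers the promised 80% at one visit. The ANCOVA gain goes beyond that target and rests on a correlation the article does not give; at r = 0.3 it is only about 3 points. All of this stands, and it limits the weight of the point.

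A reader might infer three stronger claims that the article does not support.

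- *The trial's false-positive rate is inflated.* It is not. The 7.4% to 8.8% applies only to the quarter or so of trials with moderate baseline imbalance; overall the rule is conservative.
- *The design dilutes the treatment effect.* That is true only if the group main effect is the test. Group by time is the natural reading of a pre/post design and is not diluted. For a 5-point effect at month 12 only, the main effect has about 10% to 11% power at r = 0.5 to 0.7, but the interaction has 82% to 97%, because the squared deviations again sum to 20.
- *Patients with a missed visit are dropped.* The article states no such rule. Classical repeated-measures ANOVA is often run on complete cases, but missing-data handling is commonly left to the full protocol or analysis plan. The 15% dropout is already allowed for.

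It can also be said that the t-tests supply estimates at each visit. They do so in part, but they are optional and unadjusted.

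**Conclusion.** The point holds as a recommended improvement, not as a fatal flaw. The article commits itself to adjusting for baseline only on a chance trigger and to analysing baseline as an outcome, while its own economic models adjust always. Against ANCOVA fixed in advance, the rule gives up about 3, 9 and 16 points of power at one visit for r = 0.3, 0.5 and 0.7. That is efficiency beyond the planned 80%. Power falls short of the plan only within the 2 × 5 ANOVA: for the main effect at r of about 0.6 or more, and for the interaction at r of about 0.4 or less. Because the efficacy term is not named, the article does not settle which of these applies. The figures rest on 92 completers per arm, an SD of 12.1, the assumed correlations, and, for the ANOVA, equal correlations between visits and a constant effect.

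**What to change.** In Statistical analyses, delete the pre-treatment comparison as a trigger for ANCOVA. Replace the 2 × 5 ANOVA and the unadjusted t-tests with one model for FIQ at months 1, 2, 6 and 12 that contains arm, visit, arm by visit, and baseline FIQ as a covariate in every case. Report the adjusted arm difference with its 95% CI at each visit. Analyse EQ-5D at months 6 and 12, the follow-ups at which Table 1 lists it, with adjustment for its own baseline in the same way. This brings the efficacy analysis into line with the Cost-utility analyses section.

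The cost is a change of wording. Baseline FIQ and EQ-5D are already planned covariates, so no new data, visits or patients are needed, and 109 per arm can stand.
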